### Assignment of interventions: blinding

#### Who will be blinded {17a}

The randomized, double-blind design ensures that participants as well as the research team and care providers will be blinded for the magnesium citrate intervention. The magnesium citrate and placebo identification list will only be available to concerning research pharmacies. Randomization for the additional SFOH prescription is open-label and therefore known to all involved. Data analyses will be performed before revealing the randomization code.

#### Procedure for unblinding if needed {17b}

Only in case of a suspected unexpected serious adverse reaction (SUSAR) the pharmacist will be notified by the coordinating researcher to disclose the intervention allocation of the concerning participant to the independent expert. If the independent expert develops concerns, these will be discussed with the research team and the METC if applicable.

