#### Concealment mechanism {16b}

None of the research team members have access to the ALEA randomization environment. Only the research pharmacy responsible for stratified randomization and the independent research nurse responsible for randomization of the PET-scans have individual passwords to access the randomization results. The identification list of unique randomized numbers on the medication bottles is only provided to the pharmacies. All assessments, including PWV measurement and laboratory assessments, are performed without knowledge of the allocation. Statistical analyses will be performed based on an intervention number provided by the pharmacy and only afterwards the corresponding intervention will be revealed.

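### Unblinding is limited to SUSARs and the code goes to an independent expert, so a blinded treating physician has no code-break route in an emergency

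*Protocol article*

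**What the plan says.** The protocol article has one section on breaking the blind, {17b}. It sets the trigger: "Only in case of a suspected unexpected serious adverse reaction (SUSAR) the pharmacist will be notified", with the coordinating researcher as the requester. It then sets the purpose and the recipient: "to disclose the intervention allocation of the concerning participant to the independent expert". What follows is conditional: "If the independent expert develops concerns, these will be discussed with the research team and the METC if applicable".

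Two other sections fix who knows the allocation. Section {17a} states that "participants as well as the research team and care providers will be blinded for the magnesium citrate intervention" and that "The magnesium citrate and placebo identification list will only be available to concerning research pharmacies". Section {16b} adds that "None of the research team members have access to the ALEA randomization environment". It gives passwords for the randomization results to the research pharmacy and to the independent research nurse who handles the PET-scan randomization.

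The sucroferric oxyhydroxide component is open-label ({17a}), so the point concerns magnesium citrate versus placebo alone.

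**The concern.** A blinded drug trial needs a way for the clinician treating an acutely ill participant to learn the allocation when it bears on care. Section {17b} appears to close that route in two ways. The trigger is a regulatory category (suspected, unexpected and serious) and not a clinical need. The recipient is someone assessing the event and not someone treating the patient.

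At stake is patient safety, not the validity of the comparison. Participants with an eGFR of 15 to 50 ml/min/1.73 m² take 350 mg of elemental magnesium a day, or placebo, for 24 weeks. If one of them presents with an arrhythmia, muscle weakness or a raised plasma magnesium, it matters whether the study capsules can be the source. A plasma level does not show where the magnesium came from. In a placebo participant a raised value points to some other cause that has to be looked for.

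**Working it through.** The plan gives no figure on this point to reproduce. The check is whether any section gives a treating physician access to the code.

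**Step 1: who could hold or receive the code**

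| Party | Position in the protocol article | Section |
|---|---|---|
| Treating physician / care provider | Blinded to magnesium; not named as requester or recipient | {17a}, {17b} |
| Research team | Blinded; no access to the randomization system; the coordinating researcher may ask the pharmacist to disclose to the expert | {16b}, {17a}, {17b} |
| Research pharmacy | Holds the list; discloses to the expert | {16b}, {17a}, {17b} |
| Independent PET research nurse | Can see randomization results; no role in unblinding | {16b}, {16c} |
| Independent expert | Receives the code for a SUSAR | {17b} |
| Safety board | Not established | {21a} |

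**Step 2: apply the rule to three situations**

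1. *A SUSAR.* The trigger is met and the expert receives the code. The research team and ethics committee hear of it if the expert has concerns. No step informs the treating physician.
2. *A serious reaction classed as expected.* The trigger is not met and nobody receives the code. Section {22} prespecifies arrhythmias, muscle weakness, somnolence and plasma magnesium above 1.5 mmol/L as events to record, so these are foreseen. Whether a serious case would formally be expected depends on reference safety information that is not shown.
3. *An emergency not suspected to be drug-related.* The trigger is not met and nobody receives the code, however expectedness is defined.

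The treating physician obtains the allocation in none of the three.

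**Step 3: look for another route**

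Section {11b} and the caption of Fig. 1 cover discontinuation, modification and follow-up. Neither mentions code-breaking. The figure itself is not shown.

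**Step 4: size**

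- Magnesium arms A and C: 2 × 45 = 90; 90/180 = 50%. Before any laboratory result, the blinded physician starts from an even chance.
- Cost to blinding if the route were opened, for an assumed 1% to 3% of participants needing it: 180 × 0.01 = 1.8 and 180 × 0.03 = 5.4, so about 2 to 5 participants in all. Per arm: 45 × 0.01 = 0.45 and 45 × 0.03 = 1.35.

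**The case against.** The best counter-argument is grammatical. The word *Only* could govern just the path it sits in, where the coordinating researcher asks the pharmacist to inform the expert. On that reading the sentence is silent about a physician's own request to the pharmacy and does not forbid it. The article condenses a fuller protocol (version 3.3), Fig. 1 is not visible, and emergency code-break logistics often sit in pharmacy instructions. Keeping the list with the pharmacies is ordinary concealment, and nothing says they must refuse an urgent request.

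This does not carry the point. The section is headed as the general procedure for unblinding if needed, so a reader will take its single trigger as the whole rule. An emergency route elsewhere would conflict with that sentence, and the wording would still need correcting. The article addresses the matter and settles it restrictively; it does not merely leave it to another document.

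The objections about consequence do stand in part. Capsules can be stopped without the code. Magnesium is measured at each centre's laboratory ({12}). Entry criteria limit plasma magnesium to 0.5–1.4 mmol/L and exclude QTc above 500 ms, second- or third-degree AV block and bradycardia ({10}). A physician facing a raised level would stop the capsules and treat it in any case, so the code helps mainly with finding the cause. It is also fair that the list in {22} does not define expectedness, and that the 1% to 3% rate is illustrative and says nothing about how often emergencies will occur.

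**Conclusion.** The concern holds. Read plainly, {17b} permits disclosure for SUSARs alone and to an independent expert alone. With care providers blinded under {17a}, a treating physician has no route to the code for an expected serious reaction or any other emergency. The rule reaches all 180 participants, half of them on magnesium.

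Likely harm is limited because local magnesium results, entry limits and the freedom to stop capsules all help. The estimate, power and error rate are untouched. This is a correction the trial should make, not a fault that threatens its result. The conclusion rests on the wording of the article, with Fig. 1 and the full protocol unseen, and it does not depend on the assumed code-break rate.

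**What to change.** In {17b}, delete *Only* and add wording such as: *The research pharmacy will disclose the magnesium/placebo allocation to the treating physician on request when it is needed for urgent clinical care, whether or not the event is a SUSAR.* In addition:

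- keep the independent-expert route for assessing SUSARs;
- keep outcome assessors and analysts blinded to the disclosed allocation;
- log each code break with its date and reason;
- retain unblinded participants in the intention-to-treat analysis, under the inclusion rule already in {20a}.

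The cost is a protocol wording change. The pharmacies already hold the list, and sample size and analysis stay as they are. The downside is a small loss of blinding, about 2 to 5 of 180 participants under the 1% to 3% assumption. The article describes the trial as ongoing, so the change would benefit participants still on treatment.

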### Data collection and management

#### Plans for assessment and collection of outcomes {18a}

Data collection of the primary outcome will be performed in duplicate, striving for an average PWV based on two good quality measurements during the concerning visits. Only three trained research team members will perform the PWV measurements and pre-specified quality criteria of the PWV assessment are summarized in Additional file 1. To prevent inter-assay variation laboratory measurements of T_50,_ CPPs, iPTH, cFGF-23, and Klotho will be measured centrally in one or limited batches. Since it is known freeze thaw cycles influence T_50-_test and CPP measurement, samples will be frozen directly at − 80 °C and only thawed once for central measurement.

Radiologic assessment for the Kauppila index in the context of stratification is performed by the coordinating researcher, with prior established good interrater agreement (kappa of 0.89) in a test set that was scored by the trained researcher and an experienced radiologist. All PET-scans will be performed at the Philips Vereos PET CT-scanner of the Amsterdam UMC, location VUmc. Assessment of the nuclear images of ^18^F-NaF and ^18^F-FDG PET-scans will be performed by a trained researcher after finalization of all scans to reduce intra-rater reliability.

#### Plans to promote participant retention and complete follow-up {18b}

To promote participant retention and complete follow-up, contact through phone and email is encouraged and planning of visits are confirmed through email. Also, great effort is made to combine regular laboratory or physician hospital visits with research measurements to facilitate research investment. Participants who discontinue participation after the start of the intervention will be asked to accept the T3 PWV measurement to allow ITT analysis of the primary endpoint. Protocol deviations regarding the intervention will be handled in the analyses differentiating between ITT and on treatment analyses.

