**Methods:**

In this multi-center, placebo-controlled RCT, a total of 180 participants with an estimated glomerular filtration rate of 15 to 50 ml/min/1.73 m^2^ without phosphate binder therapy will be recruited. During the 24 weeks intervention, participants will be randomized to one of four intervention groups to receive either magnesium citrate (350 mg elemental magnesium/day) or placebo, with or without the addition of the phosphate binder sucroferric oxyhydroxide (1000 mg/day). Primary outcome of the study is the change of arterial stiffness measured by the carotid-femoral pulse wave velocity over 24 weeks. Secondary outcomes include markers of calcification and inflammation, among others calcification propensity (T_50_) and high-sensitivity C-reactive protein. As explorative endpoints, repeated ^18^F-FDG and ^18^F-NaF PET-scans will be performed in a subset of participants (*n* = 40). Measurements of primary and secondary endpoints are performed at baseline, 12 and 24 weeks.

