Secondary endpoints include the difference in calcification propensity (T_50-_test), (secondary) CPP concentrations and the difference in serum/plasma concentrations of α-Klotho, C-terminal (c)FGF23, hsCRP, phosphate, and magnesium, over 24 weeks between groups. All measurements are performed in samples collected after at least 3 h of fasting. Serum for the T_50-_test and the gel filtration method based quantification of CPP measurements is frozen at − 80 °C and will be measured as described previously [24, 50]. The T_50-_test established inter-assay coefficients of variation of standards precipitating at 120, 260, and 390 min are 7.8%, 5.1%, and 5.9%, respectively [24]. These measurements will be performed as one batch without additional freeze-thaw. EDTA-plasma concentrations of cFGF23 and iPTH, and serum α-Klotho are centrally measured at the Amsterdam UMC, after storage at -80 °C at participating sites. Routine blood tests are performed directly after withdraw at the laboratories of participating centers, including plasma magnesium, phosphate, creatinine, hsCRP, calcium, albumin, potassium, hemoglobin, ferritin, lipid spectrum (low density lipoprotein (LDL), high density lipoprotein (HDL), total cholesterol and triglycerides), fasting glucose, and bicarbonate. The eGFR is calculated using the creatinine based CKD-EPI (Chronic Kidney Disease Epidemiology Collaboration) equation and plasma calcium is corrected for albumin concentration [calcium _mmol/L_ + 0.016 × (40 – albumin _g/L_)]. In addition, urinary magnesium, phosphate, creatinine, sodium, and protein are determined in 24-h urine samples at baseline and at 24 weeks of intervention. Additional parameters include demographic characteristics, anthropometric measurements, and medical history at baseline. Also seated blood pressure measurements are performed at baseline and 12 and 24 weeks with an oscillometric, automatic blood pressure monitor averaging a second and third measurement. An overview of all study measurements and procedures are presented in Table 2.

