The primary and secondary outcomes will be investigated as an ITT analysis. Within the ITT analyses, all participants will be included who have been randomized and participated in the baseline measurements and at least one follow-up visit. This analyses will be based on the initial treatment assignment and not on the treatment eventually received, thus not taking in to account dose alterations or cessation of (part of) the study intervention. Results will be considered statistically significant with a *P*<0.05 (2-sided) for the primary endpoint. For secondary endpoint analyses, we will mainly focus on effect estimates and confidence intervals. Data analysis will be performed in the SPSS 24.0 software for Windows (SPSS incorporated, Chicago, Il, USA) and StataSE 14 (StataCorp, College Station, USA) and will be performed blinded to treatment allocation.

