#### Methods in analysis to handle protocol non-adherence and any statistical methods to handle missing data {20c}

To evaluate the influence of non-adherence (treatment adherence < 80% based on pill-count), an on-treatment analysis will be performed in addition to the ITT analyses. Missing outcome variables will not be imputed since mixed models can handle these missing data. In case of missing data in relevant covariates, multiple imputation with predictive mean matching (PMM) will be performed.

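### Participants who leave the study are asked back for the T3 PWV but, as written, not for the blood sample that the secondary ITT and mediation analyses need

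*Protocol article*

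**What the plan says.** All references are to the protocol article.

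- **Retention {18b}:** participants who discontinue participation after starting the intervention "will be asked to accept the T3 PWV measurement to allow ITT analysis of the primary endpoint". One measurement and one purpose are named.
- **Statistical methods {20a}:** "The primary and secondary outcomes will be investigated as an ITT analysis". The set is defined as follows: "all participants will be included who have been randomized and participated in the baseline measurements and at least one follow-up visit". Analysis is by initial assignment, "thus not taking in to account dose alterations or cessation of (part of) the study intervention".
- **Outcomes {12}:** the secondary endpoints are T50, CPP and serum or plasma markers, ending with "FGF23, hsCRP, phosphate, and magnesium, over 24 weeks between groups". They come from samples taken after at least 3 hours of fasting.
- **Abstract, Methods:** "Measurements of primary and secondary endpoints are performed at baseline, 12 and 24 weeks".
- **Missing data {20c}:** "Missing outcome variables will not be imputed since mixed models can handle these missing data".
- **Additional analyses {20b}:** plasma magnesium and phosphate, T50, CPPs, α-Klotho and cFGF23 are among the candidate mediators of the PWV effect.

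**The concern.** The rule for collecting data after someone leaves is narrower than the analysis it feeds. An ITT analysis that disregards cessation of treatment needs values observed after cessation. Section {18b} seeks such a value for PWV and mentions none for the blood endpoints, and no other text shown does so.

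Three things are at stake.

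- **Bias.** Without a week-24 sample, the mixed model predicts the missing value from the person's own earlier values and from people who stayed, most of them on treatment. If the effect fades after leaving, the secondary estimate drifts towards the effect in those who continued. Section {20a} reads secondary endpoints mainly through estimates and confidence intervals, so such drift would bear directly on what is reported.
- **Pairing.** The abstract aims to establish how far the PWV effect runs through T50. A returned PWV without a T50 from the same visit gives that analysis an incomplete pair.
- **Recoverability.** No later analysis plan can restore a sample that was never drawn.

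**Working it through.** **1. What the 15% stands for.** Inputs from Sample size {14}: difference 1.0 m/s, SD 2.0 m/s, correlation 0.7, two-sided 0.05, power 80%, drop-out 15%.

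- SD of change = 2.0 × √(2 × (1 − 0.7)) = 1.549.
- n per group = 2 × (1.960 + 0.842)² × 1.549² / 1.0² = 37.7, so 38.
- 38 / 0.85 = 44.7, so 45; 4 × 45 = 180.

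The protocol's figures reproduce. The 15% inflates a calculation for PWV, so it is an allowance for people *without* an evaluable PWV. It is not an estimate of people who return for PWV and lack blood.

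**2. How many could be affected.** At 15%: 0.15 × 180 = 27 in total, 0.15 × 45 = 6.75 per arm. The group with PWV but no blood is 27 × a, where a is the share of leavers who accept the T3 PWV. The protocol gives no value for a. By assumption:

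- a = 0.25: 6.75 people
- a = 0.50: 13.5 people
- a = 1.00: 27 people, the ceiling at the planned rate

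**3. Ceiling on the bias.** Let m be the share of an active arm that leaves, E the effect in those who stay, and p the share of E that persists at week 24 in leavers. The effect by assignment is E × (1 − m × (1 − p)). If the model treats leavers like stayers and week-12 data add nothing, it returns E. The overstatement factor is then 1 / (1 − m × (1 − p)).

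| m | p = 0 | p = 0.5 |
|---|---|---|
| 5% | 1.05 | 1.03 |
| 15% | 1.18 | 1.08 |
| 25% | 1.33 | 1.14 |

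Only 15% is the protocol's figure; the other values of m, and both values of p, are assumptions.

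As an illustration, take the 40-minute T50 effect that the Discussion cites from an 8-week magnesium hydroxide trial (95% CI 11 to 70). With m = 15% and p = 0, the effect by assignment is 0.85 × 40 = 34 min against 40, a gap of 6 min (6/34 = 18%). With p = 0.5 it is 0.925 × 40 = 37 min, a gap of 3 min (8%).

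**4. Precision.** If 15% lack a week-24 value, the standard error of a week-24 contrast rises by 1/√0.85 − 1 = 8.5%, before any recovery through week 12.

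**5. Who has nothing to recover from.** A person who leaves before week 12 and returns only for PWV can meet the ITT definition through that visit, yet has no secondary endpoint value at week 12 or week 24. A person who leaves after week 12 still contributes a week-12 value.

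**The case against.** The case against has real force on scope and size.

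- **Leaving the study is not the same as stopping medication.** Section {18b} concerns the former. Section {11b} sends stops and modifications for safety or intolerance, with their follow-up, to Fig. 1, which is not shown. A reader might infer that everyone who stops magnesium or SFOH loses the week-24 blood sample, and that gastrointestinal intolerance would make the loss differ by arm. The text does not support this: nothing shown removes those people from the visit schedule. The unrelated drop-out examples in {14} are dialysis, transplantation and referral elsewhere.
- **Silence is not exclusion.** Section {18b} does not say that PWV is the only measurement requested. Fig. 1 or the schedule in Table 2, also not shown, could provide for blood sampling. This limits confidence to moderate. It does not remove the need for {18b} to say so, because staff following that sentence would ask for PWV only.
- **The ITT statement is not contradicted.** Section {20a} defines its set by assignment and one follow-up visit, and {20c} openly relies on the mixed model. Secondary ITT analysis remains possible under missing at random; it is weakened, not invalid. Asking leavers first for the primary endpoint is a defensible way to limit burden.
- **The size is easily overstated.** Reading 27 as the expected number with PWV but no blood reverses the meaning of the 15%, as step 1 shows. The 18% requires no persisting effect and no help from week 12. Six minutes is also small beside an interval of 11 to 70.

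What stands is that the only stated request to people who leave omits samples that the stated analyses would use.

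**Conclusion.** The mismatch is real and modest. As {18b} reads, participants who leave and accept the T3 PWV may lack week-24 values for the blood-based secondary endpoints, and the mixed model covers this only under missing at random. At the planned drop-out, 27 of 180 is an upper bound; the actual number is not given. The corresponding upper bound on overstatement of a secondary ITT effect is about 18%, and the likely figure is smaller.

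This rests on three assumptions: that T3 is the 24-week visit, which is inferred from {12} and {18b}; that the material not shown does not already request blood; and, for the bias figures, the persistence values stated in the working. The primary endpoint is unaffected and is in fact protected by the sentence in question. A reader might also conclude that ITT should be confined to the primary endpoint. That does not follow: analysis by assignment remains right for the secondary outcomes even when samples are missing. The point is a cheap improvement, held with moderate confidence.

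**What to change.** In {18b}, ask participants who discontinue participation to give the fasting blood sample for the secondary endpoints at the same T3 visit as the PWV. Make the two requests separately, so that refusing blood does not cost the PWV. If Fig. 1, Table 2 or the full protocol already provides for this, {18b} need only say so.

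The cost is a blood draw at a visit the participant is already asked to attend, plus a line in the visit instructions. The downside is slight extra burden and some refusals. The change helps only those who agree to return; people who decline T3 altogether remain missing.

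If the sample is not added, keep analysis by assignment for the secondary outcomes. State in {20a} that they use available data under missing at random, and add a sensitivity analysis that varies the effect assumed to persist in people who left.
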